**3.4.2 Proposed primary outcomes for the trial (Appendix D)**

While this pilot trial is not powered to detect meaningful differences in these outcomes, collecting data on our proposed outcomes can assess and ensure that there are no issues with the collection and completion of these measures in preparation for a future trial.

**Objective Physical Activity (Accelerometer).** A tri-axial accelerometer is a lightweight device used to measure total activity counts. The total volume of physical activity (activity counts) will be measured. This measure has the advantage of integrating the frequency, intensity, and duration of movement and combining them into an overall measure of physical activity.^61^ The sum of the total count for the day will be used and averaged over the measurement period. Total activity counts can be a better metric than the number of minutes per day spent in various physical activity intensity categories because it incorporates all levels of intensity. Recent evidence suggests that light, moderate and vigorous activity **all** have health benefits.^62^ ^63^ Ambulatory participants will wear the monitor on a waist belt on the side of the shortest residual limb which provides the most valid data in people with LLA.^64^ Wheelchair users will wear ActiGraph™ wGT3X-BT on the non-dominant arm.^65^ For wheelchair users a second ActiGraph™ placed on the rear wheel is recommended (waterproof box installed on the rear wheel using tie wraps). Participants will wear the accelerometer at all times except while bathing or swimming for a period of 7 days pre- and post-intervention and at 3-month follow-up. Only data from days in which participants wear the activity monitors for >10 hours per day will be included in the analyses as per previous approaches, including individuals with dysvascular amputation.^42^

**Self-efficacy for Exercise Scale.** A self-report measure (9 items) that includes situations that may influence physical activity participation. Participants will respond to each item on a 0 (not very confident) to 10 (very confident) scale. This is a valid measure of exercise self-efficacy in older adults.^66^

**3.4.3 Secondary outcomes (Appendix D)**

**Self Efficacy for Exercise – Dysvascular Lower Limb Amputees.** 4-item measure will be administered in addition the standardized self-efficacy for exercise measure and self-regulatory efficacy for exercise measure to address contextual factors relevant to dysvascular lower limb amputees. Items are informed by a meta synthesis of data from dysvascular lower limb amputees as well as recommendations from the literature for measuring self-efficacy.^79,83^ These items represent physical activity challenges reported by this subgroup.

**Self-Regulatory Efficacy for Exercise.** 8-item measure to assess participants’ confidence in their ability to manage their exercise. The measure pertains to behaviours necessary to self-regulate exercise over the next 4 weeks, such as scheduling exercise, planning exercise sessions, overcoming barriers that may interfere with exercise, and preventing relapse by overcoming temporary exercise lapses. Items are assessed using a confidence scale ranging from 0 per cent (not at all confident) to 100 per cent (completely confident) and in accordance with recommendations in the literature.^51, 80, 81^ These items have been used previously in exercise research, in which internal consistencies ranged from .84 to .93 (e.g., Woodgate and Brawley ^67^).

**Center for Epidemiologic Studies Depression Scale (CES-D).** The CES-D will assess participant's self-rated depressive symptoms. It is a 20-item scale that refers to symptoms in the last week. The sum of the 20 items provides a score ranging from 0-60 with higher scores indicating greater symptoms. The CES-D shows good internal consistency (Cronbach's alpha coefficient of 0.85).^68^ The CES-D is the best supported measure for diabetes^68^ and has been used in RCTs with patients with LLA.

**The Physical Activity Scale for Individuals with Physical Disability (PASIPD).** The PASIPD is a 13-item questionnaire with subscales measuring leisure time, household and work-related activities.^69^ The PASIPD has demonstrated reliability and validity in people with physical disabilities.^70^

**Leisure-Time Physical Activity for People with Disabilities Questionnaire (LTPAQ-D).** The LTPAQ-D is a self-report measure that assesses minutes of mild-, moderate-, and vigorous-intensity leisure time PA (i.e., activity that requires physical exertion and that one chooses to do in their free time performed over the past 7 days. Support for the LTPAQ’s criterion validity and test–retest reliability has been demonstrated in people with spinal cord injury and other disabilities^71^.

**Activities-specific Balance Confidence scale (ABC).** ABC is a self-report measure used to assess perceived balance confidence. The total score varies from 0 to 100, with higher scores indicating more confidence. Validity and test-retest reliability (ICC=0.91) have been shown for people with LLAs.^72^

**Prosthesis Evaluation Questionnaire - Mobility Section** (PEQ-MS). The PEQ-MS score will be used to measure the amount of difficulty completing locomotion tasks. The PEQ-MS is a reliable (ICC: 0.0.73-0.90) and internally consistent (Cronbach alpha = 0.96) measure in people with LLA.^73 74^

#### **Short Form Health Survey 12 Item survey (SF-12).** The SF-12 will be used to measure health related quality of life. Twelve items are categorized into a physical and a mental domain; the scores of the quality of life domains range from 0 to 100, with higher scores referring to higher quality of life. Several studies have reported good psychometric properties of the SF-12 including studies in older adults.^75^

**Frenchay Activities Index (FAI).** The 15-item FAI captures information on social activities. The items reflect the frequency of performance of basic and instrumental activities of daily living over three domains. The total scores range from 0 (very limited) to 45 (very active). Research demonstrates that this index is reliable and valid for use in individuals with LLA.^76^

***Descriptive Variables and Covariates:*** Demographic characteristics will be collected by questionnaire (Appendix D for participant demographics and peer demographics/profile). Participants will be asked about sex at birth (male, female or intersex), and what best describes their current gender identity (woman, man, non-binary etc). Age, employment status, education level, personal/household income, marital status, and living arrangement will also be collected. LLA characteristics will be collected: time since amputation, cause of amputation, level of amputation, co-morbid conditions, primary mode of mobility, mobility level (measured by the Amputee Single Item Mobility Measure^77^; Appendix D), cognition (measured by the Montreal Cognitive Assessment; Appendix B^78^), which will be administered by research staff, and previous participation in rehabilitation. Self-reported healthcare use (Appendix D) during the intervention will be documented.

**3.4.4 Data Collection Methods:**

All participants will be asked to complete the online questionnaires described above via REDCap. Participants will be provided with a link by email. They will be provided with the Consent Form (Appendix H), which they will be asked to read and sign before proceeding with the questionnaire. Individuals who are not able to complete the questionnaires via REDCap will be given an option to receive the questionnaire via email or by mail. To increase response rates, a research coordinator will book a time with the participant to support completion of the questionnaires (the participant will self-complete the questionnaire in REDCap; the research staff will be available to support any technical challenges). The ActiGraphTM activity monitor will be mailed to the participant with instructions on how to use it to measure total physical activity counts per day. A research coordinator will be available to support the participant via phone or Zoom/WebEx/Teams. Peer Health coaches will be provided with the Consent Form (Appendix H), which they will be asked to read and sign before proceeding with the demographics questionnaire (Appendix D), PASIPD (Appendix D) and one-on-one qualitative interview described below.

3.5 Sample Size

Since this is a pilot study, a formal sample size calculation was not performed. The recruitment of 30 participants per arm of the trial is judged to be feasible and will produce a robust amount of data while piloting across provinces in English and French (allowing a 20% drop out). This is consistent with Whitehead et. al.’s suggestions that for a trial designed with 90% power and two- sided 5% significance, pilot trial sample sizes for each treatment arm should be 25 and 15 for standardized effect sizes that are small (0.2) and medium (0.5) respectively.^84^

3.6 Recruitment

Potential participants will self-identify or be identified by a member of the research team or health professional. Individuals with dysvascular LLA will be recruited from rehabilitation hospitals with support from collaborators. Patients who have completed rehabilitation services as an inpatient or outpatient following LLA often continue to have long term follow-up appointments with the clinical team (e.g., annual visit, assessment of prosthesis, etc). Participants will be recruited from rehab clinics in the community, for example, prosthetics clinics, as well as primary healthcare clinics. Potential participants will also be recruited through community centers (e.g., Variety Village) and the networks of the research team. A research database of individuals who have indicated in past research their interest to take part in future studies will be used to identify potential participants. Individuals who have consented to being contacted for future study participation may receive a Study Invitation Letter (Appendix F).

Study posters (Appendix F for recruitment materials) will be used to recruit potential participants. Study posters will be displayed in the clinical practice areas and in outpatient amputation clinics at West Park Healthcare Centre, at rehabilitation centres/hospitals, at other clinic sites that treat individuals with a LLA (e.g., St John’s Rehab), patient organizations, community programs and organizations (e.g., Variety Village), on amputation and/or limb loss websites (i.e., Amputee Coalition of Canada), social media accounts of partners including but not limited to Amputee Coalition of Canada, newsletters, listserv/contact listservs of affiliated organizations and networks of the research team across Canada.

Social media advertisements (Appendix F) will be used to recruit potential participants. Social media ads will be displayed on West Park social media and websites (e.g. Twitter, Facebook, WP website) and other hospital, health centre, or affiliated organizations’ social media accounts and websites.

Study information sheets and study invitation letters (Appendix F) will be used to recruit potential participants. Clinicians at the rehabilitation hospitals will be informed about the study via a Study Information Sheet explaining the project. Study Invitation Letter will be provided to potential participants.

A research coordinator will have initial contact with potential participants. Individuals who self-identify and contact the study team via phone or email will receive a response from the research coordinator who will review the study information and determine their study eligibility (Appendix B for screening documents). Potential participants may have initial contact with a health professional within their circle of care or a research coordinator or administrator during an in person or virtual clinic visit. They may receive a Study Invitation Letter and may be asked by clinical or administrative staff if they agree to being contacted by a research coordinator to discuss the study.

3.7 Group Allocation

Participants will be assigned to one of two groups: intervention group and control group.

Randomization stratified by age and sex will be employed with permuted block randomization of varying block size (2 and 4) to reduce the possibility of selection bias. The allocation schedule will be created using an online tool by a person outside of the research team who is not involved in recruitment. Age is a predictor of physical activity^85^ and could be associated with the efficacy of the intervention. The age groupings (>65, 65+) are consistent with research demonstrating differences in physical activity by age in people with LLA.^101^ Stratification will be employed to ensure representation across age ranges and sex to enable investigation of these variables as effect modifiers.

An independent statistician will provide the randomization list through REDCap (REDCap Software, Vanderbilt University and National Institute of Health, USA). Upon enrolment, a study ID number will be allocated to each participant. The study ID number will be linked to the randomization list.

**3.8 Allocation concealment**

After completing the baseline assessment, the research coordinator will reveal the group allocation of the participant through the REDCap randomization list.

3.9 Masking

Due to the nature of the intervention, masking to receipt (or not) of the intervention is impossible. In this study, one assessor will collect all data. They will be masked to group allocation. We will ask participants not to disclose their group allocation during assessments.

3.10 Qualitative Interviews

For **objectives 2 and 3**, we will use a qualitative descriptive approach ^79^ to understand participants’ and peers’ experiences with IMPACT-L3. The research will be situated within an interpretive research paradigm.^80^ This component will be critical to improving the intervention and refining the protocol for the main trial. To explore perceptions of recruitment approaches, data collection procedures and measures, time burden and acceptability of program implementation (**Objective 2**), one-on-one semi-structured telephone or Zoom/WebEx/Teams interviews (Interview guides for peer health coaches and people with limb loss: Appendix G) lasting ~45-60 minutes will be conducted with participants after completion of the intervention. Participants will be asked to share their perceptions of program characteristics. For example, participants will be asked about their perceptions of Apple Watch as a tool to support behaviour change including the appropriateness of the data provided (e.g., distance) and the usability of the device. Findings will inform refinements of the intervention, **if needed** (e.g., development of a custom app to use with Apple Watch). Data will be collected until data saturation. Based on prior research^81^, we anticipate recruiting ~15-20 participants. We will sample purposively for variation in age, gender and level of amputation. **For objective 3**, we will conduct semi-structured interviews with all consenting peers to understand their experiences and identify considerations for optimizing the intervention.

**3.11 Data Analysis**

**RCT:** Descriptive statistics (mean, standard deviation, counts (percentage)) will be used to summarize continuous and categorical data, as appropriate. Questionnaire data will be analyzed in Excel and/or SPSS.

**Objective 1:** Descriptive statistics (mean, standard deviation, counts (percentage)) will be used to summarize continuous and categorical data, as appropriate. **Progression criteria:** Mellor et al. (2023)^86^ recommend using guidelines rather than rules when using progression criteria in a feasibility study, avoiding consideration of one indicator in isolation, and involvement of partners in the decision making. These principles, with the RAG (red amber green) or traffic light approach, will be used to guide the research team in determining what changes may be required to address identified challenges based on the indicators and in determining the feasibility of progression to a trial. See Table, Appendix D for specifics.

**Objective 4:** As a pilot study the analysis will be mainly descriptive. We will use the data from this pilot study to summarize overall and by group to help inform outcomes measures and sample size estimation for the main trial. The baseline activity, health and demographic characteristics and all other covariates for the intervention and control groups will be described by frequencies and percentages and mean and standard deviation as appropriate. The proposed primary and secondary outcomes will be described by mean, median, standard deviation and interquartile range. They will be visualized with box and whisker plots and histograms by intervention group and time point. Descriptive statistics and estimation, using confidence intervals, will be used to inform sample size estimation. The confidence interval will be interpreted with consideration of clinical relevance. If sufficient data, the relationship between intervention/control and the primary and secondary outcomes will be examined using linear mixed effects models including participant ID as a random effect and the observations taken at 9 weeks and 3 months as the outcome while controlling for the baseline observation. Based on stratification of sex and age in randomization, both of these variables will also be included in the models as covariates.

**Objective 5:** Cross sectional data from baseline will be used to assess construct validity of the self-efficacy for exercise questionnaire in people with dysvascular LLA and LTPAQ-D in people with dysvascular LLA. Pearson's correlation coefficients and Spearman's correlation coefficients will be used as appropriate.

We hypothesized the following associations in terms of magnitude and direction: a) a moderate positive correlation between self-efficacy for exercise, self-regulatory efficacy for exercise**,** mobility (Prosthesis Evaluation Questionnaire - Mobility Section), balance confidence (ABC), and health-related quality of life (SF-12). b) A negative correlation between self-efficacy for exercise and depressive symptoms (CES-D).

We hypothesized the following associations in terms of magnitude and direction: a) a moderate positive correlation between the LDPAQ-D and the PASIPD questionnaire, mobility (Prosthesis Evaluation Questionnaire - Mobility Section), and balance confidence (ABC).

**Qualitative Interviews:** Inductive thematic analysis will be employed to analyze qualitative interviews.^125^ NVivo software will be used for qualitative analysis. Team members will independently code four transcripts to develop a preliminary coding framework. The coding framework will be applied to four transcripts; team members will review the coding and modifications will be made to the coding framework. Codes will then be organized into categories or themes to explain the data.

**3.12 Consent Process**

Individuals who agree to participate and are eligible will have the opportunity to ask questions before reviewing and signing the Consent Form (Appendix H for consent forms). Participants will sign a Consent Form prior to taking part. Consent Forms will be signed and returned online via REDcap. Individuals who are not able to sign the Consent Form via REDCap will be given an option to sign and return the Consent Form in person, via email or by mail with a prestamped and addressed envelope. Potential participants will be given as much time as they need to decide if they would like to participate, up until the time that the study activities are scheduled to occur.

Upon obtaining consent from participants, the research coordinator will schedule the first online meeting with a blinded assessor to complete the baseline assessment. The research coordinator will log onto the online randomization system to determine the next allocation. The research coordinator will forward the participant’s contact information to schedule the first online meeting.

**3.13 Honorarium**

Participants will receive a gift certificate valued at $50 for each of the 3 assessments. Twenty participants and/or peer coaches will be asked to take part in a qualitative interview. All those who complete an interview will receive a gift certificate valued at $50.Participants will be able to keep the AppleWatch at the end of the study.

**3.14 Data Storage and Retention**

Electronic copies of the master list, consent forms and all de-identified study documents will be kept for a period of 7 years. Following this, all hard copies will be destroyed using cross-cut shredding. Electronic files will be deleted from the secure network at the end of the retention period. Audio recordings will be deleted when the study is complete.

**3.15 Privacy and Confidentiality**

Data will be password protected and stored on the West Park Healthcare Centre network drive that has firewalls and security measures in place. Hard copy records will be stored in a locked cabinet in a secure location at West Park Healthcare Centre. Access to records and data will be limited to authorized persons.

Study data will be de-identified. A master list linking participant identifying information with study IDs will be kept and stored separately from the data. Upon study completion, data collected for the purpose of recruitment will be destroyed.

Password protected audio files, identified by an identification number, will be uploaded to an account on a secure website only accessible by the transcriptionist. During transcription of audio recordings, identifying information (e.g., names, addresses, etc) will not be transcribed. The de-identified transcribed files will be encrypted and returned to the principal investigator using this secure account.

Participants will be informed that there is a possibility that their words may be cited verbatim in publications, presentations, and/or scientific meetings, that their identity will be kept confidential and that we will remove any information that may reveal their identity. Participants will be given the option to refuse the use of their words being used and quoted verbatim in publications, presentations, and/or scientific meetings and will be asked to speak to the study team prior to signing the consent form.

Participants will be informed that audio or video recording will not be permitted except by the research team. They will be asked to not record or take pictures while taking part in the study or share or stream any part of the session, including on social media. Participants will also be asked to ensure that they are in a private place when taking part in the study, where their conversation cannot be overheard.

**3.16 Personal Health Information**

Personal information (names and contact information) will only be used for administrative purposes (i.e., scheduling an interview). Demographic data will be used to describe the study population (e.g., mean age, number of male/female participants). Demographic data from individuals with amputations will include: date of birth (month and year), city of residence, country of birth, gender and sex, level of amputation, date and cause of amputation, date of admission and discharge, level of education, work status and living arrangements, comorbidities, primary mode of mobility, etc. (Appendix D).

**3.17 Benefits and Risks**

There are **minimal** additional risks to participants in the study, **which are inherent to physical activity participation**. However, the long-term benefits outweigh those risks. Telephone-based physical activity interventions have been shown to be safe for people with dysvascular LLA in RCTs. To enhance safety with physical activity (e.g. reduce risk of falls, skin problems), LLA-specific education modules will address exercise safety and peers will be trained in how to address risks.

During interviews, some participants may feel uncomfortable answering questions about their health. All participants will be informed they are not required to respond and may “pass” any questions they do not wish to address.

While the risk is low, participants could experience distress, for example, while completing assessments. If any participants exhibit signs of distress while completing the assessments, the research team will follow up with those participants and if needed, provide them with a list of mental health resources (Appendix I).

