**3.4 Outcome Measures**

Data will be collected at baseline, week 9 and a short follow-up 4 weeks later (3 months).

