**Resource Indicators:**

*Participant adherence* will be measured as the percentage of peer coaching sessions participants attend. Participants’ usage of web-based modules will be measured (i.e., number of completed modules, number of logins).

*Peer coach adherence* will be assessed by tracking the total number of peer coaching sessions attended by the peer-trainer.

*Participant and tester burden* will be measured by the amount of time it took to administer study outcomes at T1, T2, and T3 and the acceptability of the evaluation time commitment from the perspective of participants.

*Feasibility of data collection* will be evaluated as the percentage of participants with complete data on each measure at each evaluation time point. For accelerometers, the percentage of devices that were returned at baseline and follow-up (9 weeks, 3 months) and the amount of valid wear time will be assessed.

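### Section 3.17 triggers distress follow-up only on signs shown during assessments; the visible protocol states no action on a high CES-D score, although the scale is due at T1, T2 and T3

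*Protocol*

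**What the plan says.** Section 3.17 (Benefits and Risks) recognises that assessments may cause distress and gives the response: "If any participants exhibit signs of distress while completing the assessments, the research team will follow up with those participants", and, if needed, the resource list in Appendix I is supplied.

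Section 3.4.3 lists the CES-D as a secondary outcome. On recall period and scoring it says "It is a 20-item scale that refers to symptoms in the last week" and "The sum of the 20 items provides a score ranging from 0-60 with higher scores indicating greater symptoms". It gives no cut-off and names nobody to review scores.

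Section 3.4 sets data collection at baseline, week 9 and 3 months, with no exception for the CES-D.

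Section 3.4.4 has questionnaires self-completed in REDCap: "a research coordinator will book a time with the participant to support completion of the questionnaires", with staff on hand for technical problems. Those who cannot use REDCap "will be given an option to receive the questionnaire via email or by mail".

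Section 3.11 gives the CES-D analytic uses only. Under Objective 4 these are group summaries and, if data suffice, a mixed model. Under Objective 5 it is a baseline correlation with exercise self-efficacy.

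**The concern.** The safety rule relies on how a participant appears, while the trial holds a direct measure of how that participant feels. Someone may report severe depressive symptoms without showing distress, and a form returned by email or mail has no described observer. In neither case does 3.17 call for follow-up.

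The CES-D asks about the past week, so a score first read in the final analysis comes too late to help the person who gave it. The protocol's own introduction says that limb loss affects mental health, so high scores are foreseeable. At stake is participant safety, not the validity of any estimate.

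**Working it through.** The protocol gives no figure to reproduce. The check is a comparison of text, followed by simple arithmetic on scope, delay and workload.

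**Text comparison**

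1. Trigger: 3.17 refers to signs shown while the assessments are being completed. It is the only distress trigger in the visible text.
2. Observation: some staff contact appears planned at each time point. Section 3.4.1 says burden "will be measured by the amount of time it took to administer study outcomes at T1, T2, and T3", and 3.9 says "We will ask participants not to disclose their group allocation during assessments". Contact is clearest at baseline, where 3.12 describes an online meeting with a blinded assessor and 3.4.3 has staff administer the cognitive test. Visible distress may therefore be noticed.
3. Review of answers: the staff role during self-completion is technical support (3.4.4). Nobody is assigned to read the CES-D answers.
4. Other safety route: the adverse event indicator in 3.4.1 counts events tied to the intervention's physical activity, recorded by peers at coaching sessions. It does not mention CES-D scores. Controls have no coaching sessions until after follow-up (3.3).
5. Dated use of scores: Table 1 (3.23) places the outcome analysis in Year 2 Q3-Q4.

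**Scope of a score rule** (30 per arm and a 20% dropout allowance, 3.5; three time points, 3.4)

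- Participants: 30 × 2 = 60.
- No dropout: 60 × 3 = 180 forms.
- All dropout before week 9: 60 × 0.80 = 48, so 60 + 48 + 48 = 156 forms.

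**Delay if scores are first used at the scheduled analysis** (assumption)

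- Shortest: end of Year 2 Q2 to start of Year 2 Q3 = 0 months.
- Longest, to the start of the analysis window: start of Year 1 Q2 to start of Year 2 Q3 = 5 quarters × 3 = 15 months.
- Longest, to the end of the window: start of Year 1 Q2 to end of Year 2 Q4 = 7 quarters × 3 = 21 months.
- Range: 0 to 21 months.

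**Workload** (data collection Year 1 Q2 to Year 2 Q2 = 5 quarters = 15 months)

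- Per 10% of forms flagged: 0.10 × 156 = 15.6 to 0.10 × 180 = 18 contacts, or 15.6/15 = 1.04 to 18/15 = 1.20 a month.
- At 30% flagged (assumption): 46.8/15 = 3.1 to 54/15 = 3.6 a month.

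**The case against.** The strongest reply is that 3.17 deals with distress caused by the study and gives a response, while the CES-D is there as an outcome and not as a screen. Nothing in the protocol contradicts itself, and no feasibility indicator or progression decision changes. That is fair on classification. But 3.17 is a stated safety rule, and its trigger omits information the trial already holds.

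The word used is exhibit, and severe answers might be read as signs of distress. Even on that reading, the visible text asks nobody to look at the answers.

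The email or mail route is limited to people who cannot use REDCap, and device loans and technology support (3.2) should keep that group small. Weekly coaching with weekly debriefings (3.3) gives intervention participants another contact, and controls keep their usual care. These points stand and narrow the gap, but none of them acts on a score.

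Appendices B, D, H and I are not shown. A score rule could sit in one of them, although 3.17 describes Appendix I only as a list of resources. This also stands and limits confidence to medium.

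Score-based contact is also not free. Data are de-identified with a separate master list (3.15), contact details are limited to administrative use (3.16), and contacts could influence later outcomes. This stands and is included in the fix.

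**Conclusion.** The point holds as a gap in a stated safety rule that should be closed. As written, 3.17 gives no follow-up to a participant who reports severe symptoms without showing distress, or to one who returns the form unobserved. Three stronger readings are not supported:

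- A reader might infer that 156 to 180 forms, or some known number of people, would be missed. The protocol gives neither the share likely to score high nor the share using email or mail. The form count is only the scope of a rule, and the number affected is unknown.
- A reader might infer that scores will lie unread until the analysis. The protocol does not say so. The 0 to 21 months depends on that assumption and on when in Year 2 Q3-Q4 the scores are examined.
- A reader might infer that participants are unobserved throughout, or that no rule exists anywhere. Live contact is planned at least at baseline, and the unseen appendices leave the second question open.

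Collection of the CES-D at all three time points rests on the general schedule in 3.4, not on a schedule specific to that scale.

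**What to change.** 1. Total the CES-D in REDCap at submission, or on receipt for emailed or mailed forms.
2. In 3.17, make a score at or above a level set in advance by the team's clinicians a second trigger for the existing follow-up and the Appendix I list. The same clinicians set the response time.
3. Use the same scripted contact in both arms at T1, T2 and T3. The research coordinator, who already knows the allocation (3.8), should make it, not the masked assessor. The script matters because the coordinator is unmasked after baseline. Log contacts by arm and time point.
4. Amend 3.15, 3.16 and the consent form to allow re-identification and contact for this purpose.

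If an appendix already holds such a rule, a cross-reference in 3.17 is enough.

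The cost is one calculated field with an alert, small document edits and the contacts: roughly 1 a month for each 10% of forms flagged, or 3 to 4 a month at an assumed 30%.

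The downside is a possible slight effect on later CES-D and on exercise self-efficacy. Self-efficacy is a proposed primary outcome of the future trial, and the protocol expects it to correlate negatively with the CES-D. Flags at T1 are balanced by arm in expectation, because allocation is revealed after baseline. Contacts at T2 could differ by arm if the intervention changes symptoms. Contacts at T3 follow the last measurement. In a mainly descriptive pilot this is acceptable, and the log lets it be described.
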